### Data collection and management

The data collection managers for this study are full-time staff who are clinically trained but not involved in the clinical intervention process, ensuring rigorous verification and accuracy. All findings are strictly derived from original data, with error corrections on case report forms (CRFs) marked without obfuscation. Researchers meticulously document and electronically record patient information, with post-study CRFs securely stored and electronic data fixed against unauthorized modifications. Patient confidentiality is paramount, with participant follow-ups conducted telephonically upon consent.

### Data analysis

The principle of Intention-To-Treat (ITT) analysis and Per-Protocol (PP) analysis will be followed in the process of statistical analysis. Descriptive analysis will be used for the baseline characteristics of the patients in each group, data will be presented as mean or median with standard deviation or interquartile range for continuous variables and as frequency distributions for categorical variables. Two-sample t-test for quantitative data or Chi-square test for qualitative data will be performed as homogeneity test, and analysis of covariance will also be performed if an adjustment is needed for a baseline characteristic. For quantitative data that do not conform to a normal distribution, data are expressed as median (IQR). In all analyses, statistical significance will be accepted as a 2-tailed *p* < 0.05. For the primary outcome, SF-MPQ scores will be assessed by using the linear mixed-effects model with the interaction effects of time and group. Participants who do not complete the study will be treated as having no change from baseline at all times. A Bonferroni correction will be used to account for multiple comparisons. Correlation analysis will be conducted between the difference of medical infrared thermography (MIT) and the other outcome measures by the Pearson correlation analysis. All statistical analyses will be conducted with SPSS software, version 25.0 (SPSS Inc).

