**Methods and analysis:**

In this study, we enroll 60 patients experiencing CEH. The control group receives ultrasound-guided injections of GON and TON. The intervention group is treated with ultrasound localization meridian sinew tuina combined with the injection of GON and TON. Meridian sinew tuina is performed once a day for 30 min for 3 days. The primary observational index includes the Short-Form of McGill Pain Questionnaire (SF-MPQ). The Secondary outcomes include Cervical Range of Motion (ROM) and Medical Infrared Thermography (MIT). MIT is used to measure the change in skin temperature in the area of the patient’s meridian sinew tuina treatment of GON and TON before and after the intervention. There are 5 time points assessed as baseline, day 3, day 15, day 30, and day 60.

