### Sample size calculation

Derived from preliminary trial results, this study divides patients into two groups via a randomized approach. The primary efficacy endpoint is assessed using the Visual Analog Scale (VAS) scores within the Short-Form McGill Pain Questionnaire (SF-MPQ), with observed mean VAS scores of 2.40 and 3.60, alongside standard deviations of 1.10 and 1.50, for the two groups, respectively. Utilizing G*Power 3.1.9.2 for statistical calculations, with a test significance level (α) set at 0.05 and a power (1-β) of 0.9 for a two-sided test, the sample size requirement for eachup is determined to be 27 participants (32). Factoring in a 10% potential dropout rate, this necessitates 30 participants per group for both the observation and control cohorts.

$$N=2\times {\left[\left(Z_{\alpha /2}+Z_{\beta /2}\right)\times \sigma /\delta \right]}^{2}$$

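### Baseline adjustment is left conditional and undefined, and the primary mixed model does not say how it uses the baseline score; fixing each outcome's own baseline in the model would add precision at almost no cost

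*Protocol article*

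**What the plan says.** All the relevant statements but two are in the Data analysis section of the protocol article.

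- Baseline comparison: "Two-sample t-test for quantitative data or Chi-square test for qualitative data will be performed as homogeneity test".
- Adjustment, in the same sentence: "analysis of covariance will also be performed if an adjustment is needed for a baseline characteristic". No criterion for need follows, and no covariate is named.
- Significance level: "In all analyses, statistical significance will be accepted as a 2-tailed" p below 0.05.
- Primary outcome, in a sentence of its own with no condition attached: "SF-MPQ scores will be assessed by using the linear mixed-effects model with the interaction effects of time and group". No baseline covariate is named.

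The Abstract counts baseline among the assessment times: "There are 5 time points assessed as baseline, day 3, day 15, day 30, and day 60". The text does not say whether baseline is a response level in the mixed model or is handled in another way.

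The Sample size calculation section rests on a plain comparison of two VAS means and takes no credit for baseline adjustment.

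**The concern.** There are two linked problems.

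**The condition.** Under 1:1 randomisation any baseline difference is due to chance. A test of baseline homogeneity therefore cannot show whether adjustment is worthwhile; what matters is how strongly the covariate predicts the outcome. Because the plan says an adjusted analysis is done when needed, without saying what need means, the decision is taken after the data are seen. The word *also* then leaves an adjusted and an unadjusted result side by side with no stated order between them.

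**The model.** Every patient has a baseline score, but the plan does not fix how the primary model uses it. With baseline as one of the repeated response levels and the group means free at that level, the group-by-time contrast at a later visit is the difference in mean change from baseline. Its variance is at least that of the covariate-adjusted difference.

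At stake are some precision and a single prespecified estimate. The validity of the sample size is not at stake.

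**Working it through.** **Inputs from the document** (Sample size calculation): "observed mean VAS scores of 2.40 and 3.60"; "standard deviations of 1.10 and 1.50, for the two groups, respectively"; "with a test significance level (α) set at 0.05 and a power (1-β) of 0.9 for a two-sided test"; 27 per group, raised to 30 for 10% dropout.

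**Assumed, because the document does not give them:** the correlation r between baseline and follow-up VAS, taken as 0.3 to 0.5 (entry at VAS 5 or more restricts the baseline range, which argues against a high value); and the ratio k of baseline SD to follow-up SD, taken as 1.0 down to 0.5. All figures treat the analysis as one follow-up comparison, which simplifies a five-time-point model.

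**Step 1. Reproduce the plan.** Common SD = √[(1.10² + 1.50²)/2] = √1.73 = 1.315. Standardised difference d = 1.20/1.315 = 0.912. The two-sided t-test at 0.05 (noncentral t) has power 0.897 at 26 per group and 0.908 at 27. So 27 is confirmed, and 27/0.9 = 30.

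**Step 2. Baseline as covariate.** The variance is multiplied by 1 − r², so the effective d is 0.912/√(1 − r²), with one degree of freedom less.

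| r | 1 − r² | effective d | power at 27 per arm |
|---|---|---|---|
| 0.3 | 0.91 | 0.956 | 0.932 |
| 0.4 | 0.84 | 0.995 | 0.948 |
| 0.5 | 0.75 | 1.053 | 0.967 |

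**Step 3. Baseline as an unconstrained response level (change score).** The variance is multiplied by 1 + k² − 2rk. This exceeds 1 − r² by (k − r)², so it is never smaller and is equal only when k = r.

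| r | k | variance factor | power at 27 per arm |
|---|---|---|---|
| 0.3 | 1.0 | 1.40 | 0.794 |
| 0.3 | 0.85 | 1.2125 | 0.848 |
| 0.3 | 0.7 | 1.07 | 0.889 |
| 0.3 | 0.6 | 1.00 | 0.908 |
| 0.5 | 1.0 | 1.00 | 0.908 |
| 0.5 | 0.7 | 0.79 | 0.959 |
| 0.5 | 0.5 | 0.75 | 0.967 |

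The change-score contrast can fall well short of the planned 90%, match it, or equal covariate adjustment. The document does not say which applies.

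**Step 4. What conditional adjustment would do, if the condition were a baseline t-test at p < 0.05.** This rule is an inference, not text. It was simulated with 200,000 trials per setting, 27 per arm, one baseline covariate and one follow-up.

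| | r = 0.3 | r = 0.5 |
|---|---|---|
| Adjustment triggered | about 5% | about 5% |
| Power, conditional rule | 0.909 | 0.915 |
| Power, always adjusted | 0.926 | 0.964 |
| Type I error, conditional rule | 0.047 | 0.043 |
| Type I error, either result may be claimed | 0.063 | 0.073 |

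The simulated power for adjustment is slightly below Step 2 because it includes the cost of chance imbalance in the covariate. Under this rule most of the available gain is lost, because adjustment is rarely triggered. Type I error rises only if both analyses are run and the better one may be claimed.

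**The case against.** The best defence is that the primary analysis is not conditional at all. The mixed model has its own sentence, the ANCOVA is an additional analysis described alongside the baseline comparisons, and baseline is one of the five time points. The primary model may therefore already use the baseline score unconditionally, and if its baseline means are constrained equal, nothing is lost. Detailed covariate lists are also commonly left to an analysis plan, which is not shown here. Much of this stands, and it rules out several stronger readings:

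- *A reader might infer that p < 0.05 on a baseline test triggers adjustment.* The sentence invites that reading but does not say so; need could be judged on clinical or prognostic grounds. Without the trigger, however, there is no rule at all, which leaves more discretion.
- *A reader might infer that the choice of primary model depends on the baseline tests.* Nothing in the text makes it so.
- *A reader might infer that chance imbalance in pain passes straight into the primary estimate.* If baseline is a response level, the contrast subtracts the baseline difference. It may over-correct, but that is a different fault.
- *A reader might infer an inflated type I error.* A strictly followed test-then-adjust rule is slightly conservative.
- *A reader might infer that the trial is underpowered.* It was sized without adjustment, and 27 per arm gives 0.908. The 0.79 figure needs a correlation of 0.3 and equal SDs; the VAS entry threshold makes a smaller baseline SD plausible.

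The defence does not remove the core. The document itself writes down a conditional adjustment without a criterion or covariate, and an analysis plan that followed it would carry the fault forward. No constrained baseline is specified either.

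**Conclusion.** The point holds as a worthwhile improvement, not as a flaw that threatens the trial. The condition for ANCOVA is undefined and depends on observed data, and the role of baseline in the primary mixed model is not stated. For assumed correlations of 0.3 to 0.5, prespecified adjustment raises power from 0.908 to about 0.93 to 0.97 at 27 per arm. Against a change-score contrast the gain ranges from nothing to about 14 percentage points (0.932 − 0.794), depending on the correlation and the SD ratio. These sizes rest on assumed values and on a single-follow-up simplification. The direction does not: covariate adjustment is at least as efficient as the change score at any correlation, and more efficient than ignoring baseline whenever the correlation is appreciable. At a correlation near zero it costs one degree of freedom.

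**What to change.** In the Data analysis section:

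1. Describe baseline characteristics by group and drop the homogeneity tests.
2. Replace the conditional ANCOVA with a prespecified primary model: a linear mixed model on the post-baseline scores with group, visit, group-by-visit, the outcome's own baseline score and baseline-by-visit. An equivalent model that keeps baseline as a response but constrains the group means to be equal there would also serve.
3. Apply the same form to the other SF-MPQ components, range of motion and thermography, each with its own baseline.
4. Label any further adjusted analysis as sensitivity, with its covariates named in advance.

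The cost is a few sentences of text. Baseline is already an assessment time, so there is no new data collection, and the sample size need not change.

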## Methods and design

### Trial design

This study is designed as a single-center, randomized, parallel-controlled trial. Participants will be randomly allocated to one of two groups: the control group, which will receive ultrasound-guided injections into the greater and third occipital nerves (GON and TON), or the intervention group, which will undergo ultrasound-localized meridian sinew tuina in conjunction with GON and TON injections, maintaining a 1:1 ratio. The effectiveness of these treatments will be assessed at five distinct time points: at baseline, 3 days post-treatment commencement, 15 days post-treatment conclusion, and 30 and 60 days following the end of treatment.

This trial has been registered with the China Clinical Trial Center, bearing the identifier ChiCTR2300076128. It is committed to following the guidelines as set forth by the SPIRIT (Standard Protocol Items: Recommendations for Interventional Trials) statement (27) and adheres to the ethical standards outlined in the Declaration of Helsinki (28) (Figure 1) (see trial flow in Figure 2).

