### Recruitment

Recruitment will target patients with CEH at the Tuina Department of Guilin Municipal Hospital of Traditional Chinese Medicine, Guangxi, China. Recruitment strategies include hospital-based poster displays and social media outreach, particularly through platforms like WeChat.

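### Scoring every non-completer as unchanged from baseline at all visits discards observed scores and does not fit the dropout allowance behind the stated 90% power

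*Protocol article*

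**What the plan says.** The Data analysis section sets the primary model: "SF-MPQ scores will be assessed by using the linear mixed-effects model with the interaction effects of time and group". Assessments are at baseline and days 3, 15, 30 and 60. The next sentence gives the only missing-data rule in the document: "Participants who do not complete the study will be treated as having no change from baseline at all times". The same section names both intention-to-treat and per-protocol analyses.

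The Sample size calculation section works from the VAS within the SF-MPQ, "with observed mean VAS scores of 2.40 and 3.60, alongside standard deviations of 1.10 and 1.50, for the two groups, respectively", with alpha "set at 0.05 and a power (1-β) of 0.9 for a two-sided test". The number per arm "is determined to be 27 participants", and then: "Factoring in a 10% potential dropout rate, this necessitates 30 participants per group". Allocation is described as "maintaining a 1:1 ratio".

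The inclusion criteria require a VAS of at least 5. No baseline mean or SD is given. The Discussion accepts that neither practitioners nor participants can be blinded.

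**The concern.** Two parts of the plan do not fit together.

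First, the rule is single imputation of the baseline value, and its wording reaches every visit, including visits the participant attended. A likelihood-based mixed model can use a partial record as it stands, so real data are lost without need.

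Second, the sample size section assumes that a non-completer leaves the analysis and only reduces its size. Under the rule, that person stays in with a value well above the arm's planned mean. This pulls the two arm means together and widens the spread. Raising 27 to 30 does not allow for either effect.

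At stake are the stated power of the primary comparison and, if the arms lose clearly different numbers, the treatment estimate itself.

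**Working it through.** **Inputs from the protocol article.** Means 2.40 and 3.60, SDs 1.10 and 1.50, two-sided alpha 0.05, power 0.90, 27 evaluable and 30 enrolled per arm, 10% dropout (Sample size calculation). Baseline VAS at least 5 (Inclusion criteria).

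**Assumptions.** The lower mean belongs to the intervention arm, since the text does not say. Both planned means lie below the entry threshold, so they are taken as follow-up values. The entry VAS and the SF-MPQ VAS are taken to share a 0–10 scale. The baseline mean B is equal in both arms and is varied from 5 to 8.

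**1. The plan's own figure.** Pooled SD = √[(1.10² + 1.50²)/2] = √1.73 = 1.315, so the standardised difference is 1.20/1.315 = 0.912. The noncentral t calculation gives power 0.897 with 26 per arm and 0.908 with 27, so 27 reproduces. Then 27/0.9 = 30. The benchmark is therefore 90.8% with 27 completers per arm, or 93.5% if all 30 are observed.

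**2. Difference under the rule, 10% dropout in each arm.**
- Intervention mean: 0.9 × 2.40 + 0.1 × B
- Control mean: 0.9 × 3.60 + 0.1 × B
- Difference: 0.9 × 1.20 = 1.08, whatever B is

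**3. Variance under the rule.** Each arm is a mixture. With no spread in baseline, its variance is 0.9 × SD² + 0.1 × 0.9 × (B − mean)². At B = 6:
- Intervention: 0.9 × 1.21 + 0.09 × 3.6² = 1.089 + 1.166 = 2.255
- Control: 0.9 × 2.25 + 0.09 × 2.4² = 2.025 + 0.518 = 2.543
- Pooled SD: √[(2.255 + 2.543)/2] = 1.549, against 1.315 in the plan

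**4. Power, t-test at one visit, 30 per arm.** The simulated range covers exactly 3 non-completers per arm and a 10% chance for each patient. Baseline SD is 0, with SD 1 also run at 6 and 7 (values limited to 5–10). Each setting used 20,000 trials.

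| Mean baseline VAS (assumed) | Difference | Pooled SD | Power by formula | Power by simulation |
|---|---|---|---|---|
| 5 (entry minimum) | 1.08 | 1.396 | 83.8% | 83–87% |
| 6 | 1.08 | 1.549 | 75.7% | 73–80% |
| 7 | 1.08 | 1.741 | 65.7% | 64–70% |
| 8 | 1.08 | 1.959 | 55.5% | 55–57% |

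Every row is below the 90.8% benchmark. A repeat on the change-from-baseline scale, with the SD of change assumed equal to the stated SDs, gave values in the same ranges.

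**5. Unequal dropout, 6 of 60 in total (intervention vs control).**

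No true effect, both follow-up means assumed 3.0 with SD 1.315, and leavers assumed to have done as well as completers had they stayed. The artificial difference is (control leavers − intervention leavers)/30 × (B − 3.0).
- 1 vs 5: 4/30 × (B − 3.0) = 0.27 at B = 5 and 0.53 at B = 7. Simulated type I error is about 10–14%.
- 2 vs 4: 2/30 × (B − 3.0) = 0.13 to 0.27. Type I error stays below 5% (4.4% at B = 5, 2.8% at B = 7).

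Planned effect, B = 6:
- 4 vs 2: intervention (26 × 2.40 + 4 × 6)/30 = 2.88 and control (28 × 3.60 + 2 × 6)/30 = 3.76. The difference is 0.88, with simulated power 54–57%.
- 2 vs 4: 2.64 and 3.92. The difference is 1.28, with simulated power 92–94%.

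**The case against.** **No-change imputation is a recognised and usually cautious convention in pain trials.** If leavers really do return to baseline, 1.08 is the true effect over all randomised patients, and a missing-at-random model would be the optimistic one. This stands as a reason to keep the rule as a sensitivity analysis. It does not justify replacing scores that were observed, and it leaves the sample size section inconsistent with the rule.

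**The sentence may mean only the visits after a participant leaves.** That reading would keep the observed scores, but the words do not say so. Anyone who leaves before a given visit would still enter that visit at the baseline value.

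**The power figures come from a single-visit t-test, not from the mixed model with its time-by-group interaction.** This stands. The t-test is the basis of the protocol's own sample size, which makes the comparison fair, but the mixed model's power needs within-subject correlations that are not given.

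**The per-protocol analysis may partly serve as a check that leaves non-completers out.** That may be so, but it does not alter the rule for the main analysis.

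**Two stronger readings are tempting.** A reader might infer one definite power figure. The documents do not support one, because the size depends on an unstated baseline mean. A reader might also infer that control patients will leave more often and so favour the intervention, given that "Recruitment will target patients with CEH at the Tuina Department". That line says only where patients are found. Three daily 30-minute sessions could just as well raise dropout in the intervention arm, where the rule works against tuina. Mild imbalance (2 vs 4) does not inflate type I error.

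**Conclusion.** The concern holds in conditional form. As worded, the rule overwrites observed scores in a model that could use them, and it contradicts the assumption behind raising 27 to 30. The fall in the difference from 1.20 to 1.08 needs only the planned 10% dropout in each arm, equal baseline means, and leavers scored at baseline. Power on the plan's own single-visit basis is below 90% at every baseline mean tried. It ranges from 83–87% at the entry minimum down to 55–57% at a mean of 8, and where the trial would fall in that range cannot be known from the document.

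Bias from unequal dropout is a risk, not a prediction. It can run either way and needs a clear imbalance. Calling the resulting difference spurious also assumes that leavers would have done as well as completers.

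A reader might go on to infer that the protocol must rank intention-to-treat over per-protocol, add delta-adjusted analyses or prescribe continued assessment after suspension. Those go beyond this error, and the first two are commonly left to an analysis plan.

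**What to change.** Remove the no-change sentence from the primary analysis. State instead that the linear mixed model is fitted by likelihood to all randomised patients, using every observed visit without imputation, under missing at random. Keep no-change imputation as a sensitivity analysis, applied only to visits that are actually missing.

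The cost is a change of wording and one extra model run, with no additional patients or visits. The drawback is that the primary result then rests on missing at random, which the data cannot prove. The retained sensitivity analysis checks it.

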### Observational indicators

#### Primary observational indicators

##### Short-Form McGill Pain Questionnaire (SF-MPQ)

Pain evaluation is performed using the SF-MPQ, a globally recognized instrument for describing and quantifying pain experiences (29). The SF-MPQ consists of three main components: the Pain Rating Index, which assesses the quality of pain; the Visual Analogue Scale for headache, offering a subjective measure of pain intensity; and the Present Pain Intensity section, which provides a snapshot of the current pain level.

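### Plain Bonferroni is valid, but Holm's step-down rule gives the same 5% family-wise protection and can only add rejections; the gain is about 0 to 9 points of power per true effect

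*Protocol article*

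**What the plan says.** The protocol article, Data analysis, fixes one multiplicity rule: "A Bonferroni correction will be used to account for multiple comparisons". The same section sets the significance level for all analyses ("In all analyses, statistical significance will be accepted as a 2-tailed" p below 0.05) and analyses the primary outcome with a linear mixed model containing a time-by-group interaction. It does not say which comparisons form the family or how many there are.

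Two families suggest themselves:

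- **Visits.** The abstract says "There are 5 time points assessed as baseline, day 3, day 15, day 30, and day 60", which leaves four post-baseline comparisons.
- **Components.** The section on the primary indicator says "The SF-MPQ consists of three main components", which would give three comparisons.

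The Sample size calculation section uses a single VAS comparison, "with a test significance level (α) set at 0.05 and a power (1-β) of 0.9 for a two-sided test".

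**The concern.** Single-step Bonferroni holds every comparison to 0.05/m, even after others in the family have been rejected. Holm relaxes the threshold after each rejection, needs no further assumption about dependence, and keeps the family-wise error at 5%. For testing, Bonferroni can therefore miss a true effect that Holm would find, and never the reverse.

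With 60 patients, and claims that may rest on the pattern across several visits or pain measures, what is at stake is how often true effects beyond the strongest one are declared non-significant. Validity is not at stake.

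**Working it through.** **Inputs from the article (Sample size calculation).** "observed mean VAS scores of 2.40 and 3.60, alongside standard deviations of 1.10 and 1.50"; the number per group "is determined to be 27 participants"; and "Factoring in a 10% potential dropout rate, this necessitates 30 participants per group".

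**Assumptions, because the article gives no figure.** Number of comparisons m = 3 or 4; correlation between comparisons 0.3 to 0.7; number of comparisons with a true effect from one to all.

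**Step 1: reproduce the stated sample size.**

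- SD = √((1.10² + 1.50²)/2) = √1.73 = 1.315
- d = (3.60 − 2.40)/1.315 = 0.912
- Two-sample t-test (noncentral t), two-sided 0.05: power is 0.897 at 26 per arm and 0.908 at 27. So 27 reproduces, and 27/0.90 = 30.

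(The printed formula, with Z at β/2, would give 32. That is a separate matter and is not used here.)

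**Step 2: thresholds, for m = 4.**

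- Bonferroni: 0.05/4 = 0.0125 for every comparison.
- Holm, from the smallest p-value upward: 0.05/4 = 0.0125, 0.05/3 = 0.0167, 0.05/2 = 0.025, 0.05, stopping at the first failure.

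Each Holm threshold is at least as large as Bonferroni's, so Holm rejects whatever Bonferroni rejects. The first threshold is the same, so the chance of at least one rejection is the same by construction.

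**Step 3: power per comparison under Bonferroni at 27 per arm.** The same t-test at 0.05/m gives 0.848 (m = 2), 0.807 (m = 3) and 0.774 (m = 4).

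**Step 4: Holm against Bonferroni.** This was a simulation of m equicorrelated normal outcomes with two-sample t-tests, 27 per arm, and at least 20,000 trials per setting. The gain is in average power per true effect, in percentage points, over correlation 0.3 to 0.7.

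| Family | True effects | Gain |
|---|---|---|
| m = 4 | all four at d = 0.912 | about 7 to 9 |
| m = 3 | all three at d = 0.912 | about 6 to 7 |
| m = 4 | three of four | about 4.4 to 5.4 |
| m = 4 | fading: 100, 75, 50, 25% of d | about 4.4 to 4.8 |
| m = 4 | all four at half of d | about 3.2 to 4.5 |
| m = 3 | two of three | about 2.6 to 3.2 |
| m = 4 | two of four | about 2 to 2.5 |
| m = 3 or 4 | one only | about 0.1 to 0.2 |

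At correlation 0.5 with all effects true, average power goes from 0.808 to 0.874 for m = 3 and from 0.772 to 0.857 for m = 4. The chance that every comparison is significant goes from 0.623 to 0.786 and from 0.505 to 0.731. With no dropout (30 per arm), m = 4 and all effects true, the gain is 7.3 points at correlation 0.5 and 6.1 at 0.8.

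**Step 5: what does not move.** For m = 4 at correlation 0.5 with all effects true, the chance of at least one rejection is 0.962 under either rule. Under the global null, both rules have the same family-wise error (3.7 to 4.8%). In mixed settings with some true nulls, Holm's simulated family-wise error did not exceed about 0.048.

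**The case against.** The strongest reply is that nothing here is wrong. Bonferroni is prespecified, holds under any dependence and respects the stated 5% level; preferring another valid procedure does not expose a defect. That stands, and it is why this is graded as an improvement only.

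Three further objections also stand in part.

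- **Size.** A reader might infer that the trial simply gives away 6 to 9 points of power on each comparison. The article does not support that. It gives the effect once, for VAS, with no visit named. Nothing says that the same effect holds at all four visits or for all three components. After one short treatment course, an effect that fades by day 60 is at least as plausible, and the gain is then about half as large.
- **Family.** The three-component family is a reading of the text, since the sample-size section names VAS as the primary efficacy endpoint. Which comparisons are corrected may be set out in a fuller document, so its absence from the article is not held against the plan.
- **Intervals.** Bonferroni tests have simple matching simultaneous confidence intervals and Holm tests do not. Keeping tests and intervals coherent is a legitimate reason to stay with Bonferroni, although the article does not give it.

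What the reply does not show is any setting in which Bonferroni rejects more than Holm at the same error level.

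**Conclusion.** The point holds as an optional efficiency gain. For hypothesis testing, Holm uniformly dominates the stated rule at the same 5% family-wise error. Assuming 27 per arm, d = 0.912 and correlation 0.3 to 0.7, the gain per true effect is about 6 to 9 points if all three or four comparisons carry the design effect, about 4 to 5 if three of four do or the effect fades, about 2 to 2.5 if two of four do, and about 0 if only one does.

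Two stronger inferences should be resisted. The plan does not fail to control error. Nor does the choice between the rules decide whether the trial finds anything at all: the chance of at least one rejection is identical, and the single time-by-group interaction test is untouched. That the 90% power was computed at an unadjusted 0.05 is a different matter, which changing the procedure does not settle.

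**What to change.** Before unblinding, replace the Bonferroni sentence with:

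> Wherever multiple comparisons are corrected, including the between-group comparisons at the four post-baseline visits for SF-MPQ, p-values will be adjusted by the Holm step-down procedure at an overall two-sided 5% level within each family.

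This wording keeps the present scope of the correction. A sentence confined to the primary outcome would silently drop any correction now intended for range of motion, thermography or the correlations. Holm cannot be applied reproducibly without knowing m, so the comparisons in each family should be listed wherever the full analysis is specified.

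**Cost:** one sentence, with no extra patients or data; the adjustment needs only the unadjusted p-values from the planned models. The downside is in the intervals: they would be reported unadjusted or at the Bonferroni level, and may occasionally disagree with the Holm test (for example, a Holm-significant difference whose Bonferroni interval includes zero). The report should say which kind is shown.
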